### Serious adverse events

A serious adverse event (SAE) is defined as any untoward medical occurrence that:Results in deathIs life-threateningRequires inpatient hospitalisation or prolongation of existing hospitalisationResults in persistent or significant disability/incapacityIs an important medical event, which may require intervention to prevent one of the previously listed outcomes

In this study, all SAEs will be reported regardless of suspected causality.

### Adverse event and serious adverse event reporting

Separate Case Report Forms will be developed to record AEs and SAEs. SAEs occurring from the time of commencement of study treatment to 72 h post intervention will be reported to the coordinating centre by faxing the supplied SAE Form within 24 h of site study staff becoming aware of the event. In this pilot trial, all deaths up to day 30 will be reported as a SAE. Coordinating centre staff will be responsible for following up SAEs to ensure that all details are available. It is the responsibility of each site to inform their Human Research Ethics Committee (HREC) of all SAEs which occur at their site, in accordance with local requirements.

All SAEs will be forwarded to the chair of the DSMC within 24 h of receipt at the REFRESH coordinating centre. As detailed in the Patient Information and Consent Form, any injury or complication occurring as a result of trial participation is to be reported to the study team who will arrange all necessary medical treatment. In Australia, Medicare will provide any required medical treatment, free of charge, in a public hospital.

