Randomisation	Eligible participants in whom a consent process has been commenced will be randomised to either the fluid-volume restricted or the fluid-liberal (standard-care arm)
Randomisation procedure	• Eligibility assessment and randomisation conducted by clinical staff with support by research personnel (in person or by telephone)
	• Computer-generated randomisation sequence
	• Real-time web-based randomisation
	• 1:1 randomisation in blocks of 2 or 4
Blinding	• Un-blinded to patients and to treating team
	• Blinding of laboratory staff and data analysts
Data collection methods	• Paper CRF completed for each participant
	• CRF populated by research staff in real time or from clinical record
	• Subsequent data entry into secure database by trained research assistant
	• Audit of data entry against source documentation
Data collected	• All fluids administered pre-randomisation
	• All fluids administered post randomisation – 6 h (recorded hourly)
	• All fluids administered over 6–24 h
	• Urine output to 24 h
	• Vital signs at enrolment and hourly until 6 h
	• Antimicrobials – agent, dose and time administered
	• Corticosteroid administration
	• Source of sepsis (suspected/proven)
	• Charlson Comorbidity Score
	• Microbiological/serological results from samples obtained in first 24 h
	• Sequential Organ Failure Assessment (SOFA) score at admission and at 24 h
	• Acute Physiology and Chronic Health Evaluation (APACHE) II score (peak first 24 h)
	• Acute Kidney INjury (AKIN) score up to 7 days
	• Study blood sampling at enrolment (T0), 3 h (T3), 6 h (T6) and 12–24 h (T24)
Statistical analysis	• Intention-to-treat analysis
	• Statistician blinded to treatment allocation
Data and safety monitoring	• DSMC – emergency physician, intensive care physician, statistician
	• SAE reporting to study coordination centre within 24 h
	• DSMC review all SAE
	• Periodic data review by DSMC and recommendations to PI in event of study conduct of SAE issues
	• Trial coordinator will monitor trial conduct at each site at regular intervals
Ethics and governance	• HREC approvals obtained for all sites
	• Clinical governance (site-specific authority) procedures in place for all sites
	• Any subsequent protocol amendments to be submitted to lead ethics site with appropriate dissemination to participating study sites
	• The study will be conducted in accordance with GCP
Consent	• Where possible, prospective informed consent will be obtained

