### Adverse events

Adverse events (AEs) are defined as any untoward medical occurrence in a patient administered an investigational intervention which does not necessarily require to have a causal relationship with this intervention.

Patients with severe sepsis in the ED and ICU commonly have aberrations in laboratory values, signs and symptoms due to the severity of their underlying disease and the impact of standard therapies [33]. These will not necessarily constitute an AE unless they require significant amelioration or are considered to be of concern in the investigator’s clinical judgment. AEs include all unexpected and/or untoward medical events experienced by the patient *which are not part of the expected course of sepsis*.

The following will be considered AEs, regardless of study treatment allocation and subsequent intervention required:Extravasation of peripherally administered noradrenaline infusion (whether or not any tissue injury occurred)CVC-related complicationsBleedingInadvertent arterial puncturePneumothoraxThrombosisInfectionArterial catheter-related complications, including thrombosisAny other event that is considered to be of concern by the site investigator

The AEs listed above will be recorded from the time of commencement of study treatment to 72 h post intervention. CVC-related complications, including infection, will be considered an AE for as long as the CVC remains in situ.

All AEs will be reported, irrespective of treatment allocation to the chief investigator and/or the REFRESH Management Committee and then forwarded to the chair of the DSMC.

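### A serious, non-fatal central-line complication after 72 h counts as an AE while the line is in place, but falls outside the SAE route and its 24-h deadlines

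*Protocol article*

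**What the plan says.** Four places in the Protocol article set the rules.

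- **Adverse events.** The general window is 72 h: "The AEs listed above will be recorded from the time of commencement of study treatment to 72 h post intervention". One class of event is then exempted from it: "CVC-related complications, including infection, will be considered an AE for as long as the CVC remains in situ". All AEs go to the chief investigator and/or the management committee and then to the DSMC chair. No time limit is given for either step.
- **Serious adverse events.** Seriousness follows the usual criteria, which include a threat to life and a prolonged hospital stay. The section ends: "In this study, all SAEs will be reported regardless of suspected causality".
- **Adverse event and serious adverse event reporting.** "SAEs occurring from the time of commencement of study treatment to 72 h post intervention will be reported to the coordinating centre", and this must be done "within 24 h of site study staff becoming aware of the event". The next step is also timed: "All SAEs will be forwarded to the chair of the DSMC within 24 h of receipt at the REFRESH coordinating centre". The coordinating centre follows up SAEs. One exception to the 72 h is stated: "In this pilot trial, all deaths up to day 30 will be reported as a SAE".
- **Table 1 (Aim, design and setting), data and safety monitoring row.** It gives SAE reporting to the coordinating centre within 24 h and "DSMC review all SAE", and states no 72-h limit for either.

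Both treatment-arm descriptions allow central access by CVC or by PICC. The exemption in the Adverse events section names only the CVC.

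**The concern.** The authors judged that central-line harm can outlast 72 h, since they removed the 72-h limit for those events when defining AEs. The SAE rule does not carry that exemption over. For central-line complications, the window for reporting an event as serious is therefore shorter than the window for recording it at all.

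This matters because of how the trial is monitored. The section on trial administration and the DSMC plans no formal interim analysis and no stopping rules, and leaves the timing of periodic reviews to the DSMC chair. The DSMC can suspend or halt recruitment, so prompt individual SAE reports are an important part of its timely information. Table 1 also names assessing the safety of the restricted approach as a purpose of the pilot. A count of SAEs that omits later serious line complications would be an incomplete safety summary for the larger trial that this one is meant to inform.

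**Working it through.** The documents give no figure to reproduce here, and no sample-size or event-rate formula applies. The check is to follow one type of event through the rules.

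**Windows side by side**

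| Event | Counted as an AE | Reported as an SAE if serious |
|---|---|---|
| Listed AE other than a CVC complication | to 72 h | to 72 h |
| CVC complication, non-fatal | while the CVC is in place, no 72-h limit | to 72 h |
| Death | not needed for this check | to day 30 |

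Only in the second row is the SAE window shorter than the AE window.

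**A CVC complication after 72 h with the line still in place**

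1. *Not serious.* It is an AE and goes by the AE route. The rules agree.
2. *Serious but not fatal*, for example an infection on day 5 that prolongs the stay. It is an AE under the in-place rule and meets the SAE definition. It occurred after 72 h and is not a death, so the reporting section does not ask for an SAE form. Only the AE route remains.
3. *Fatal by day 30.* It is reported as an SAE through the stated exception. The rules cover it.

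The gap is case 2.

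**What case 2 loses**

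- SAE route: 24 h from site awareness to the coordinating centre, then 24 h from receipt to the DSMC chair. If receipt is immediate, that is at most 24 + 24 = 48 h from awareness to the chair.
- AE route: the same destination, with no deadline at either step.
- The SAE form and the coordinating centre's SAE follow-up are also not triggered, and the event does not enter the SAE count.

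**Does the start of the 72-h clock matter?** The text does not say whether 72 h after the intervention runs from its start or from the end of the 6-h study period. The limit is then 72 h, or 72 + 6 = 78 h, after study treatment starts. Day 5 begins at 4 × 24 = 96 h, so the example lies outside the window on either reading.

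**How many events?** This cannot be derived. The document gives no duration of line placement, no complication rate and no expected proportion of participants with a central line. CVC insertion rate and timing are themselves process-of-care outcomes.

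**The case against.** The strongest reply is that nothing is hidden from the DSMC. All AEs are forwarded to its chair, and the DSMC reviews all deaths and adverse events. The reporting section adds that any injury or complication resulting from participation is to be reported to the study team, and case report forms are submitted at the end of the hospital stay, day 28 and day 90. This stands: it would be wrong to say that late line complications are lost. What is missing is the deadline, the SAE form and follow-up, and classification as an SAE.

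Two of the supporting texts are also weaker than they look. The sentence that all SAEs will be reported concerns causality and says nothing about time, so it does not by itself contradict a 72-h window. Table 1 is a summary and may simply omit a limit stated elsewhere. Both points are fair. The conflict rests on the in-place rule set against the SAE window, and Table 1 adds to the ambiguity.

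A reader might infer more, and the document does not support it:

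- *That the restricted arm is made to look safer.* That arm can reach vasopressors earlier, so greater line exposure is plausible. But both arms have the same vasopressor and line steps, no line use by arm is given, AEs are listed irrespective of allocation, and the events are kept as AEs. No bias is shown.
- *That SAE reporting should match the day-28 organ-support outcomes.* Nothing requires a safety window to equal an outcome horizon, and the protocolised intervention lasts 6 h.
- *That arterial-catheter and extravasation events show the same contradiction.* For arterial-catheter events, the AE and SAE windows both end at 72 h, which is a consistent choice. Whether an early extravasation that later becomes serious is covered depends on how the time of occurrence is read.

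**Conclusion.** The point holds in a narrow form. A non-fatal central-line complication that occurs after 72 h, while the CVC is in place, and that meets the SAE definition is an AE under one section but outside the SAE route of another. It therefore reaches the DSMC without a deadline and is not captured as an SAE.

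This follows from the text alone and assumes only that sites apply the reporting section as written. Its size in events is unknown. Fatal cases to day 30 are covered, no difference between arms is shown, and the primary outcome and its analysis are unaffected.

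It is not a detail left to another document, because the article states both windows and they do not agree. It is a modest safety-reporting inconsistency, worth correcting because it concerns a class of harm that the protocol itself chose to follow beyond 72 h.

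**What to change.** Reconcile Table 1, the Adverse events section and the reporting section.

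1. **Reporting section.** Add a second exception beside the one for deaths: any central-line complication that counts as an AE under the Adverse events section and meets the SAE definition is reported by the same 24-h SAE route for as long as the line is in place, including after 72 h.
2. **Adverse events section.** Word the in-place rule to cover a PICC as well as a CVC, since both arms allow either.
3. **Table 1.** Refer to these windows, so that its SAE entries are read with the same limits.

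A general extension of SAE reporting to discharge or day 28 is not needed to remove the inconsistency. Seriousness is reported without a causality filter, and the AE list includes any event of concern to the site investigator, so such an extension could bring in many background sepsis events.

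The cost is a short amendment, a matching line in the SAE form instructions and a few additional SAE forms. At submission of the article 42 of 100 participants had been enrolled, so an amendment at that point would have applied from enrolment to the remaining 100 − 42 = 58.

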### Strategies to achieve adequate enrolment

An education package has been developed for staff at enrolling sites. In addition, individual site visits (physical or virtual) will be undertaken at trial commencement. The Trial Steering Committee will meet by teleconference at least monthly and review enrolment rates and discuss strategies to maximise these. Several sites have dedicated research nurses in the ED who will actively screen for eligibility. Finally, the trial will be publicised by presentations at academic meetings and via social media platforms – e.g. Twitter @REFRESH_Trial.

## Discussion

### Significance

This will be the first randomised trial examining the question of fluid volume in the early resuscitation of adult patients with sepsis-associated hypotension in a mature health care system with access to advanced critical care. This is an important clinical question given the findings of observational studies and the FEAST trial [18]. Given the universal use of fluids to manage this condition, superiority of a restricted approach is likely to have significant clinical and economic impact. A recent trial demonstrated the feasibility of a restricted-volume approach to sepsis in ICU [34]. However, the median volume of fluid administered prior to randomisation was over 4 l. By recruiting patients in the ED, at the earliest point in the course of their care, we aim to investigate very early resuscitation. This essentially replicates the approach of the FEAST trial [18], but in an industrialised country with access to advanced critical care.

Undertaking such a trial in the ED setting presents considerable challenges. Unlike the ICU, patients present to the ED with undifferentiated illness. Sepsis is a highly heterogeneous condition. Often the onset of illness is insidious, and the clinical presentations highly variable. In addition, sepsis is a clinical syndrome and there is a lack of a standard diagnostic test. Nevertheless, the ARISE trial [32] demonstrated that the identification and enrolment of patients with sepsis into a clinical trial in Australian EDs is possible.

The REFRESH trial will provide essential feasibility and mechanistic plausibility data to support a large-scale clinical trial. A multicentre pilot will allow assessment of the feasibility of delivering the protocol in a range of settings. For example, participating sites are inclusive of both tertiary referral centres and urban general hospitals. A number of sites have substantial research infrastructure, including research nurses within the ED, whereas at other sites the trial will rely on enrolments by clinical staff. Metrics, such as rates of recruitment of eligible patients and adherence to the trial protocol, will be assessed as part of the feasibility objectives. All this information will be utilised in designing the optimal protocol for a trial that is clinically acceptable and operationally achievable.

### Limitations

An open-label design confers challenges but is unavoidable given the nature of the trial intervention. Potential bias arises due to the treating clinician being aware of the treatment allocation. The pragmatic nature of the trial allows for some latitude for the clinician to determine fluid volumes within set parameters; however, it is difficult to control for individual behaviours and treating physician preference for one approach over another. An additional potential challenge may be the reluctance to give fluid in the standard-care arm on the basis of perceived potential harms (the rationale for the trial). To counter this, regular feedback and educational sessions with clinicians will occur throughout the trial. For this pilot trial, the primary feasibility outcomes are objective measures (e.g. fluid volumes, processes of care). Clinical outcome measures are also objective and pre-specified, e.g. mortality, organ failure. However to minimise any potential risk of bias, a physician-investigator will adjudicate clinical outcomes blinded to group allocation. Similarly, laboratory analyses will be conducted in blinded fashion.

### Stakeholder engagement and dissemination of findings

The investigator team comprise clinicians in emergency medicine and intensive care who have substantial experience in conducting research among critically ill patients. The REFRESH protocol has been developed over an 18-month period during which extensive consultations took place. The protocol has been informed by practical feedback including from clinician groups locally at participating sites, and following presentation at the Australian and New Zealand Intensive Care Society Clinical Trials Group (CTG), and the Annual Scientific Meeting of the Australasian College for Emergency Medicine (ACEM). The REFRESH trial has received formal endorsement from the ACEM CTG.

The trial results will be of wide interest to the global emergency and critical care communities. It is anticipated that the results will be used to inform the design of, and secure funding for, a large-scale clinical trial to evaluate patient-centred outcomes. The results of the trial will be submitted for publication in a suitable international journal. A writing committee will be convened from among the Trial Steering Committee. Authorship criteria will be according to the International Committee of Medical Journal Editor definition.

### Trial status

At the time of submission the REFRESH trial has enrolled 42 of its planned 100 participants.

## Abbreviations

ACEM: Australasian College for Emergency Medicine
AE: Adverse event
AKIN: Acute Kidney Injury Network
APACHE: Acute Physiology And Chronic Health Evaluation
ARISE: Australasian Resuscitation in Sepsis Evaluation
CVC: Central venous catheter
DSMC: Data Safety Monitoring Committee
ED: Emergency department
FEAST: Fluid expansion as supportive therapy
HREC: Human Research Ethics Committee
ICAM: Intercellular adhesion molecule
ICU: Intensive care unit
IL-6/10: Interleukin-6/10
IPPV: Intermittent positive-pressure ventilation
IV: Intravenous
MAP: Mean arterial pressure
NGAL: Neutrophil gelatinase-associated lipocalin
NIV: Non-invasive ventilation
PICC: Peripheral intravenous central catheter
SAE: Serious adverse event
SBP: Systolic blood pressure
SOFA: Sequential Organ Failure Assessment
SpO_2_: Peripheral transcutaneous oxygen saturation
SSC: Surviving Sepsis Campaign
VCAM: Vascular cell adhesion molecule
